### Sample size calculation: effect size and statistical power

The proposed sample size of 36 subjects is anticipated to be further reduced by follow-up attrition, resulting in an approximate final study sample of 28-31 subjects. Based on the proposed sample size, the study is sufficiently powered (80%) to detect only very large effects (*d *= 1.0 using Cohen's terminology [23]), assuming a 2-tailed test with alpha at 0.05. Given the reduced power of the study to detect smaller effects than this, inferential statistics will play a relatively limited role in this pilot study, with the focus primarily descriptive in nature.

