### Participants

Participants will be approximately 36 young people, aged 15-24, who are being discharged from EPPIC. There are currently around 300 young people registered with EPPIC, between 10 and 20 of whom are discharged per month. For the purpose of the study protocol we have assumed that on average 12 people will be discharged per month and that 50% (n = 6) will consent to participate. This would mean that 3 people would be recruited to the treatment group and 3 people would be recruited to the control group per month. The study has a 6-month recruitment period which would give us a sample of approximately 36, 18 in the treatment and 18 in the control group. It is anticipated that the sample would be reduced by follow-up attrition, resulting in an approximate final study sample of 28-31 subjects. Please see Figure 1.

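### The 80% power for d = 1.0 is stated for the 36 recruited; the 28-31 expected at follow-up give about 72-77%

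*Protocol article*

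**What the plan says.** The section on sample size calculation opens with the recruited number and its expected loss: "The proposed sample size of 36 subjects is anticipated to be further reduced by follow-up attrition". It then puts a figure on what will remain: "resulting in an approximate final study sample of 28-31 subjects". The next sentence gives the power: "Based on the proposed sample size, the study is sufficiently powered (80%) to detect only very large effects". The effect is specified as d = "1.0 using Cohen's terminology", and the test conditions are given as "assuming a 2-tailed test with alpha at 0.05". The section then concludes that, because smaller effects could not be detected reliably, inferential statistics will have a limited role and the focus will be mainly descriptive.

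The Participants section gives the same two numbers. It derives 36 from about 12 discharges a month, 50% consent and six months of recruitment, giving "a sample of approximately 36, 18 in the treatment and 18 in the control group". It then repeats the expected loss: "It is anticipated that the sample would be reduced by follow-up attrition, resulting in an approximate final study sample of 28-31 subjects".

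The Statistical methods section says that groups are compared on the key outcomes at follow-up, and that baseline differences will be taken into account if necessary. Neither power nor a detectable effect is given for 28-31 participants.

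**The concern.** Power belongs to the number of people who contribute an outcome. Here the outcome comparison is made at follow-up, and the protocol forecasts 28-31 people at that point. The power sentence nevertheless uses the 36 recruited, directly after the sentence that forecasts the loss.

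This pairing of d = 1.0 with 80% power is the only operating characteristic the article gives. It also marks the boundary below which the protocol says its power is reduced. If the boundary is drawn for 36 and the comparison is made on 28-31, power is already below 80% at d = 1.0 itself. Anyone who uses the figure to judge the trial's sensitivity, or to plan the larger study mentioned in the Discussion, would start from a slightly favourable number.

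**Working it through.** **Inputs.** From the sample size section: two-sided alpha 0.05, power 80%, d = 1.0, 36 proposed, 28-31 expected finally. From the Participants section: 18 + 18, so 1:1 allocation. The implied attrition is 1 − 31/36 = 13.9% to 1 − 28/36 = 22.2%.

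**Assumptions.** The protocol does not name the test behind its figure. I take an unadjusted two-sample t-test on one outcome, with losses spread about evenly over the groups.

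**Formula.** With group sizes n1 and n2, df = n1 + n2 − 2, noncentrality λ = d·√(n1·n2/(n1 + n2)), and critical value c, the 97.5th percentile of t with df degrees of freedom:

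power = P(T > c) + P(T < −c), where T is noncentral t with df and λ.

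**Step 1: the protocol's own figure.** For 18 + 18 and d = 1.0, λ = √(18·18/36) = 3.00 and df = 34. Power is 83.0%. Solving for the effect that gives exactly 80% yields d = 0.96, which rounds to 1.0. So d = 1.0 at 80% is a fair rounded description of 36 analysed participants.

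**Step 2: the number needed.** For 17 + 17, λ = √8.5 = 2.92 and power is 80.7%. For 16 + 16, λ = √8 = 2.83 and power is 78.1%. The threshold is therefore 34 analysed.

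**Step 3: the expected follow-up sample.**

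| Analysed | Split | λ at d = 1.0 | Power at d = 1.0 | d detectable at 80% |
|---|---|---|---|---|
| 36 | 18/18 | 3.00 | 83.0% | 0.96 |
| 34 | 17/17 | 2.92 | 80.7% | 0.99 |
| 31 | 16/15 | 2.78 | 76.7% | 1.04 |
| 30 | 15/15 | 2.74 | 75.3% | 1.06 |
| 29 | 15/14 | 2.69 | 73.7% | 1.08 |
| 28 | 14/14 | 2.65 | 72.1% | 1.10 |

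The chance of missing a true d = 1.0 is thus about 23-28%, against the 20% that the stated power implies.

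**Step 4: sensitivity to the method.**
- *Normal approximation:* 16 per group (32) would suffice. Power is 79.5% at 31 and 75.4% at 28, so it comes close at the top of the range but does not reach 80%.
- *One-sided test:* 85.8% at 31 and 82.4% at 28, but the protocol specifies two tails.
- *Uneven losses:* 18 against 13 gives 75.7%; 18 against 10 gives 68.5%.
- *Baseline adjustment:* no baseline-outcome correlation is given. As an assumption, a correlation r multiplies the effective d by 1/√(1 − r²). With r = 0.3, power is 76.1% at 28 and 80.5% at 31. With r = 0.5, it is 83.7% and 87.4%.

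**Step 5: precision.** The half-width of a 95% interval for the difference, in SD units, is c·√(1/n1 + 1/n2). For 16/15 this is 2.045 × 0.359 = 0.735. For 14/14 it is 2.056 × 0.378 = 0.777.

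**The case against.** The strongest reply is that the sentence is accurate as labelled. It names its base as the proposed sample size, which the sentence before defines as 36, and for 36 the figure reproduces. The expected number of completers is printed in the same paragraph, so nothing is hidden. This stands. A reader might infer that the 80% is an arithmetic slip, and the documents do not support that. A reader might also infer that the claim holds at exactly 36 and nowhere else. That too is wrong, since 34 analysed participants are enough.

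Second, the gap is small. The protocol reports d to one decimal; 1.04 at 31 participants still rounds to 1.0, although 1.06-1.10 at 28-30 rounds to 1.1. All of these remain very large effects, and the sample numbers are described as approximate. This stands as an argument about severity.

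Third, baseline adjustment could restore 80% at d = 1.0. Setting 1/√(1 − r²) equal to the detectable effect gives an assumed correlation of about 0.28 at 31 participants or 0.42 at 28. So it goes too far to say that the completed trial cannot have the stated power under any analysis. But adjustment is only conditional in the Statistical methods section, no correlation is given, and it is not the calculation stated.

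Fourth, a reader might infer that the trial is undersized by mistake, or that its conclusions are at risk. The documents do not support this. Power did not set the sample size, and the protocol uses the figure to argue for restraint in inference, not to claim adequate sensitivity.

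**Conclusion.** The point holds as a minor correction. The power statement uses the recruited number, while the comparison will be made on the 28-31 participants the protocol expects at follow-up. For that sample, power at d = 1.0 is about 72-77%, a shortfall of roughly 3 to 8 percentage points, and 80% power applies to d of about 1.04-1.10. This rests on a two-sided 0.05 unadjusted t-test, one outcome and roughly equal groups. No two-sided unadjusted calculation that I tried reaches 80% anywhere in the expected range; the normal approximation at 31 comes closest.

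No design decision changes. The sample size follows from recruitment flow, the planned comparison is mainly descriptive, and the corrected figure strengthens the protocol's own conclusion about limited power.

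**What to change.** Restate the power sentence for the expected follow-up sample, for example:

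*With 28-31 participants followed up, the study has 80% power (two-sided alpha 0.05, unadjusted two-sample t-test, one outcome, roughly equal groups) to detect d of about 1.04-1.10; power for d = 1.0 is about 72-77%.*

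The figure for 36 may stay beside it if it is labelled as the case of no attrition (83% at d = 1.0). Given the descriptive focus, it would help to add that the 95% confidence interval for a standardised difference will have a half-width of about 0.74-0.78 SD. If a baseline-adjusted analysis is intended, give its power together with the correlation assumed.

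The cost is one sentence and a slightly less favourable number, with no added participants and no change to the conduct of the trial.

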### Statistical methods

A range of descriptive statistics will be used to compare the groups on key outcome measures at follow-up, including level of engagement and treatment adherence, perceived social support and service satisfaction. Additionally, symptom and outcome measures will be assessed, including suicidal ideation/behaviour, severity of depression and functional outcome. The extent of any baseline differences on these measures will also be examined and taken into account if necessary. Furthermore, identification of the key components of an effective peer support program based on the perspective of the client will provide vital qualitative information which will be used to design future programs.

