## Methods/design

### Aims and hypotheses

The overall aims of this study are to test the feasibility and effects of a 6-month peer support intervention delivered to young people with FEP from approximately 3 months prior to discharge from a specialist treatment service, and continuing for 3 months post-discharge. We also aim to identify what participants want from a peer support program at this time. If the program proves effective and acceptable to participants, we aim to develop a treatment manual to support future programs.

The hypotheses are that when compared to treatment as usual (TAU) the peer support intervention will lead to: 1. Increased engagement and treatment adherence among people being discharged from the Early Psychosis Prevention Intervention Centre (EPPIC) and who are being referred on to alternative services; 2. Increased perceived social support; 3. Increased quantity and improved quality of information provided; 4. Increased service satisfaction; 5. Reduced risk of suicide; and 6. High levels of satisfaction with peer support role for recipients and peer support workers.

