## Discussion

This paper describes the development of a randomised-controlled trial which aims to pilot a peer support program among young people who are being discharged from a specialist FEP treatment centre. Whilst intuitively attractive, there is little evidence regarding the potential benefits of peer support for young people with FEP currently available at this time. There is also little evidence regarding what young people want from a service such as this, and whether or not there are potential benefits for the peer support workers as well as the study participants. Thus, in addition to the primary outcomes of interest, it is hoped that this pilot study will provide some indication as to what kinds of support young people require at this time and whether or not it is realistic to expect other young people to provide this.

Through participation in the program all peer support workers will receive training and experience that will be of benefit to them once the study is complete. In addition, protocols and a treatment manual will have been developed that will be sustainable once the research is complete. However if the research indicates that the program is of benefit the study team will seek continued funding in order that the program can continue and be further tested with a larger sample.

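### The article names only descriptive comparisons, with no interval for the between-group difference, yet ties next steps to the programme being effective or of benefit; at 28-31 participants descriptive summaries alone cannot support that judgement

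*Protocol article*

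**What the plan says.** All references are to the protocol article.

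- **Method.** Statistical methods: "A range of descriptive statistics will be used to compare the groups on key outcome measures at follow-up". Baseline differences are to be examined and allowed for if that seems needed. No confidence interval, standard error or test for the difference is named.
- **Reason for the method.** The sample size section states that "the study is sufficiently powered (80%) to detect only very large effects" and draws the consequence that "inferential statistics will play a relatively limited role in this pilot study, with the focus primarily descriptive in nature". It does not say which inferential statistics remain, or for which outcomes.
- **Question to be answered.** Aims and hypotheses sets out directional effects against treatment as usual. Outcomes defines the primary outcomes as whether the intervention leads to better results than control in four domains: engagement and adherence, perceived social support, service information, and service satisfaction.
- **Use of the answer.** Aims and hypotheses: "If the program proves effective and acceptable to participants, we aim to develop a treatment manual". Discussion: "if the research indicates that the program is of benefit the study team will seek continued funding". The Discussion sentence goes on to give two purposes for that funding: keeping the programme running and testing it again in a larger group.

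**The concern.** The questions are about between-group effects, and the next steps are worded as depending on the answers. The only method named for answering them does not, by itself, show how precisely each difference is known. Standard deviations would count as descriptive statistics, but they describe the spread among participants, not the precision of the difference between groups.

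Low power is a sound reason to drop significance verdicts. It is also the reason to show the uncertainty of the difference. Without it, a moderate-looking difference favouring peer support may be reported as benefit, or a near-zero one as no effect, when the data rule out neither. The decision to seek funding, and the planning of a larger trial, could then rest on a point estimate taken at face value.

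**Working it through.** **Inputs**
- From the sample size section: 36 participants, 28-31 after attrition, two-sided alpha 0.05, 80% power, d = 1.0.
- From Participants: 18 per arm at randomisation.
- Assumed, because the article does not give them: a near-equal split at follow-up (14/14 for 28, 15/16 for 31), roughly normal outcomes, no baseline adjustment, and one measure per domain. Differences are in SD units. The 0.5 SD and 0.3 SD yardsticks are illustrative, since the article sets no minimum worthwhile difference.

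**1. The plan's own figure.** The two-sample t-test needs 16.7, so 17, per arm for d = 1.0 at 80% power, or 34 in total (16 per arm by the normal formula). At 18/18 the power is 83% and the detectable d is 0.96. The stated d = 1.0 for 36 participants is therefore reproduced. At 28-31 analysed, power for d = 1.0 is 72-77% and the detectable d is 1.10-1.04.

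**2. Standard error of the difference**, SE = sqrt(1/n1 + 1/n2):
- 14/14: sqrt(1/14 + 1/14) = 0.378, 26 df
- 15/16: sqrt(1/15 + 1/16) = 0.359, 29 df

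**3. Chance differences with no true effect**, P(|d| >= c) = 2 × P(t > c/SE):

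| Observed difference | 28 analysed | 31 analysed |
|---|---|---|
| At least 0.5 SD, either direction | 0.197 | 0.175 |
| At least 0.5 SD, favourable only | 0.099 | 0.087 |
| At least 0.3 SD, either direction | 0.435 | 0.411 |

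**4. Width of a 95% interval**, t(0.975) × SE: 0.777 SD at 28 and 0.735 SD at 31. An observed 0.5 SD would have an interval of about -0.28 to 1.28 (28 analysed) or -0.24 to 1.24 (31 analysed). An observed zero would run from about -0.78 to 0.78 or -0.74 to 0.74.

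**5. Four primary domains.** The chance that at least one shows a favourable difference of 0.5 SD or more, with no true effect, is 1 - (1 - 0.099)^4 = 0.34 at 28 and 1 - (1 - 0.087)^4 = 0.31 at 31 if the domains are independent. By simulation with a common correlation between 0.7 and 0.3, it is about 18-28%.

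**6. A decision rule to avoid.** One might let the programme go forward whenever the interval is compatible with a worthwhile benefit. With a worthwhile effect of 0.5 SD, the upper limit reaches 0.5 whenever d exceeds 0.5 - 0.777 = -0.277 (28 analysed) or 0.5 - 0.735 = -0.235 (31 analysed). With no true effect that happens in about 77% and 74% of trials, including some that favour control.

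**The case against.** **Inference is not excluded.** A reader might infer that no measure of uncertainty will be reported, or that bare group means will be set side by side. The article says neither. It keeps a limited role for inference, allows for baseline differences, and is a condensed account whose full protocol or analysis plan could specify intervals. This stands, and the absence of a detailed list of statistics is not the fault. What remains is a mismatch within the article: the method it names, and its stated reason for it, do not fit the judgements of effectiveness it goes on to describe.

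**The consequence is softened.** A reader might infer that a chance result leads straight to adoption, or that the manual hangs on the group comparison. The funding step includes a further, larger test. The Discussion also says, without condition, that a manual will have been developed, and the Intervention section says contact logs and feedback will inform it. This stands too, so the manual is a weak example of harm. The funding step is the firmer one, because it also covers continuing the programme and follows from a finding of benefit.

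**The limitation is disclosed.** The article admits it can detect only very large effects and calls itself a pilot. That is fair and justifies the descriptive emphasis. It does not tell the reader how benefit would be recognised.

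**Conclusion.** The point holds as a mismatch between method and use, not as a claim that uncertainty is ruled out. At 28-31 analysed, a difference of 0.5 SD or more on one outcome arises by chance in about 17-20% of trials with no true effect (9-10% favourable), and the 95% half-width is about 0.74-0.78 SD. Neither benefit nor its absence can be judged from descriptive summaries alone at that precision.

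The figures rest on the assumptions listed with the inputs; adjusting for baseline would narrow the intervals. The change is worth making, but the descriptive focus itself need not be abandoned.

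**What to change.** In Statistical methods, add: *Each key between-group difference at follow-up will be reported as an estimate with its 95% confidence interval (a risk difference with its interval for binary outcomes). No statement of effectiveness, or of no effect, will be made from group summaries or point estimates alone.*

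Reword the conditional sentences in Aims and hypotheses and in the Discussion so that next steps rest on feasibility and acceptability, with the effect estimates and their intervals used to inform a larger trial. Do not substitute a rule that the interval be compatible with a worthwhile benefit: step 6 shows that most trials with no true effect would pass it at 0.5 SD.

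The cost is a few sentences and an interval column in the results table, with no new data. The downside is that the results will look less certain.

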### Safety and supervision

All PSWs will receive the same training prior to commencing the program. This will comprise an introduction into peer support work, information regarding local services, training in managing clinical aggression, Mental Health First Aid Training [24] and suicide risk management training (Applied Suicide Intervention Skills Training (ASIST)) [25]. In addition a treatment protocol will be prepared by the PSW supervisor and the research team which will clearly set out what the intervention will and will not include, and what the PSW is and is not expected to do. Fortnightly supervision sessions will be provided by the supervisor for all PSWs. These sessions will be used to provide basic supervision but also to monitor the nature of the PSW contacts and to identify any ongoing training needs.

In addition an on-call system will operate staffed by the PSW supervisor and members of the research and clinical team. All PSWs will be required to ensure that the on-call supervisor knows of the time and location of their visit. The PSW will be required to SMS the supervisor when the visit is complete. If there were any problems or concerns they will be required to telephone the on-call worker and these will be dealt with appropriately.

Regular team meetings will be held in order that any difficulties can be dealt with promptly and to facilitate close liaison between the peer support workers, the clinical representatives and the research team. This will also allow for ongoing discussion about the nature of the PSW contacts with participants. It will also ensure that the research team are fully aware when discharge planning commences and the exact point of discharge for each participant and when the intervention commences and finishes. Similarly this will enable the research team to inform the peer support workers once the baseline assessment is complete and the intervention can begin.

## Discussion

This paper describes the development of a randomised-controlled trial which aims to pilot a peer support program among young people who are being discharged from a specialist FEP treatment centre. Whilst intuitively attractive, there is little evidence regarding the potential benefits of peer support for young people with FEP currently available at this time. There is also little evidence regarding what young people want from a service such as this, and whether or not there are potential benefits for the peer support workers as well as the study participants. Thus, in addition to the primary outcomes of interest, it is hoped that this pilot study will provide some indication as to what kinds of support young people require at this time and whether or not it is realistic to expect other young people to provide this.

Through participation in the program all peer support workers will receive training and experience that will be of benefit to them once the study is complete. In addition, protocols and a treatment manual will have been developed that will be sustainable once the research is complete. However if the research indicates that the program is of benefit the study team will seek continued funding in order that the program can continue and be further tested with a larger sample.
